### Sample size calculation

Sample size calculation was performed for the main outcome, the time to first bowel movement using the R environment version 3.0, and the “gsDesign” and “samplesize” packages.

In a previous study, coffee consumption reduced the time to bowel movement after surgery from 74 ± 21 h to 60 ± 21 h (mean ± standard deviation) [10]. In that study, one cup of coffee (containing 80 to 130 mg of caffeine [19]) was administered three times a day. The published results of this study were based on a mix of open and laparoscopic procedures in patients with and without epidural analgesia. Because we have access to the raw data of this study, possible bias by the type of surgical access and epidural analgesia could be eliminated. Using the raw data (per-protocol analysis), the time to first bowel movement for patients after open colon resection with epidural analgesia was 61.5 ± 18.5 h for the 21 patients receiving coffee versus 72.5 ± 19.5 h for the 25 patients receiving the placebo. The number of patients with laparoscopic surgery was too low to derive meaningful data. The standardized effect size of caffeine was estimated to be 0.5 (a reduction of 10 h with a standard deviation of 20 h). Even if the absolute time to bowel movement after laparoscopic colectomy differs from the time after open surgery, the standardized effect size for both types of access can be assumed comparable. In addition, a standardized effect size of 0.5 is usually considered to be of clinical importance for study outcomes.

Assuming a power of 80 % with a two-sided alpha of 0.05 (hypothesis: superiority of caffeine), a total of 144 patients (N = 48 in the placebo, and N = 96 in the treatment arms) are necessary to detect a standardized effect size of 0.5 for a 1:2 ratio of placebo versus caffeine (for this analysis, the two caffeine arms (100 mg/200 mg) are pooled). Assuming a 20 % dropout rate (withdrawal rate), 180 patients are required for the study. Patients who withdraw from the study before receiving the first study treatment (caffeine, placebo, or radio-opaque markers) will be replaced by other patients. Otherwise no replacement for dropout or withdrawals will be performed. A bootstrap simulation using the raw data mentioned above confirmed the parametrically determined sample size.

### Data collection and monitoring

Patients will be hospitalized during the whole study (due to the colectomy). Thus, study participants are under steady monitoring by surgeons and regular nursing staff. Furthermore, a dedicated study nurse will collect data from the patients’ records and will ask the patients directly for the key endpoints (time to first flatus, time to bowel movement, etc.). This study nurse will also deliver and collect the questionnaires from the patients and will help them with the questionnaires if the patient so wishes.

Data will be collected with a custom-made software with extensive data-entry checks (numerical data are restricted to plausible ranges, and categorical data entry is performed via pull-down menus or option buttons). Entry forms for questionnaires have the same layout as the questionnaires themselves. Thus, correct data entry can be confirmed by simple pattern comparison. Data entry is recorded in an audit log, the data set can be restored to the state of the last five close events, and an overnight backup to a remote server is performed daily.

### Patient safety

Since patients are hospitalized during the whole study period, they are well monitored and adverse events can be quickly treated. Most people in the Western world consume caffeine-containing beverages on a regular basis. The lower dose of caffeine used in this study (100 mg) corresponds to approximately 1 cup of filtered coffee. Furthermore, numerous medications contain caffeine as an additional ingredient (e.g., painkillers); thus, one can assume that the consumption of caffeine, even at the higher dose of 3 × 200 mg is very safe for the patients. However, few data exist on the effect of caffeine on elderly (most patients presumably will be older than 50 years) [20, 21], and none, on the consumption right after abdominal surgery.

Most of the documented side effects are not very severe and are usually observed after higher dosages. Documented side effects are muscle tremor (>200 mg), sleeplessness, restlessness, headache (>200 mg), irritability, gastrointestinal complaints, tachycardia, and, in rare cases, allergic reactions. Doses of 100 mg are not recommended in the case of tachyarrhythmia and liver cirrhosis. All these side effects and restrictions have been considered in the exclusion criteria [22].

While all available knowledge suggests that the consumption of caffeine after surgery should be safe, unexpected adverse effects cannot be ruled out with certainty. In case a patient should be harmed by the trial treatment, the sponsor obtained a liability insurance to cover any damages caused by the trial participation (as required by Swiss law).

The safety and efficacy of the study treatment is being monitored by a data and safety monitoring committee consisting of three members who are independent of the study. The members are specialists in hepatology, emergency medicine, and surgery.

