### Study population

Study participants will be recruited from patients of the Department of General, Visceral, Endocrine and Transplantation Surgery scheduled for laparoscopic elective colon and upper rectum resection. The indication for surgery (oncologic or nononcologic) is not a selection criterion.

In particular, the patient has to fulfill the following criteria to be considered for study inclusion:The patient is scheduled for elective laparoscopic colectomy (right or left hemicolectomy, segmental resection, extended hemicolectomy, sigmoid resection, or upper rectum (anastomosis higher than 7 cm above the anal verge)).The patient’s age is equal to or over 18 years old. As long as the patient is fit for surgery, no upper age limit exists.The patient gives informed consent before surgery.

The following criteria will exclude the patients from trial participation:Participation in another concurrent interventional trialNeed for a stoma (colostomy or ileostomy) or reversal of a stoma, if the patient had complete bowel obstructionKnown hypersensitivity or allergy to caffeine/coffeeExpected lack of compliance (patient is notorious for not following medical instructions, like taking medications as prescribed, or following necessary diets)American Society of Anesthesiologists (ASA) Physical Status Score of IV or VImpaired mental state or language problemsAlcoholism or drug abusePrevious extensive abdominal surgery (any open or laparoscopic abdominal surgery except laparoscopic appendectomy, cholecystectomy, or hernia repair)Inflammatory bowel diseaseClinically significant cardiac arrhythmia (patient suffers from physical complaints or is on regular medication)Cardiac insufficiency (like the previous criterion as safe guard against the effects of caffeine)Pregnancy, lactation, or childbearing potential without using adequate contraceptionIntake of opioid analgesics, or steroids > 5 mg/day for ≥ 7 days before surgeryUnder antidepressive medicationLiver cirrhosis or compromised liver function (MELD score > 15) (Caffeine is metabolized in liver cells, and impaired liver function would result in a prolonged half-life of the caffeine.)

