The final decision to include (i.e., to randomize) the patient in the trial will be made at the end of the surgery. The following criteria have to be fulfilled:No major change of the planned surgery (like conversion to open, unplanned placement of a stoma, additional resections of adjacent organs, or other major unplanned procedures)No epidural anesthesia used during or after surgery

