### Study withdrawal and stopping medication

After randomization, the patients can withdraw at any time if they own wish without giving any reason.

Study treatment will be stopped for the following reasons:Any adverse event resulting from surgery that might interfere with the study drug or might lead to meaningless endpoint data (e.g., organ failure, anastomotic failure, or postoperative dementia). Due to the complexities of postoperative morbidity, no list of fixed criteria will be established. If such an event occurs before the first study medication will be taken, the patient will be withdrawn from the study and replaced by another patient.Serious adverse events occur that are definitively or probably related to the study drug.Tachycardia, defined as a pulse of over 120/min three times within 1 hour, occurs.In the investigator’s opinion, continuation of the treatment is detrimental to the patient’s well-being.

Unless the patient wishes to withdraw from the study, all scheduled examinations will be performed as planned as long as they are meaningful and do not pose an unnecessary burden to the patient (e.g., no X-ray examination will be performed if treatment is stopped very early or if the patient has multiple vomiting events during the first 3 days postoperatively). Thus, stopping the medication does not automatically constitute withdrawal from the study.

The investigator can withdraw a study patient if a reoperation before the return to normal bowel function is required, an epidural analgesia was placed, if there are signs of renal insufficiency or an acute renal insufficiency, or if the patient clearly is not compliant (repeated refusal to take study medication or is consuming caffeine-containing beverages or food).

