### Study outline

If a suitable patient is identified during the outpatient visit in preparation of surgery, he or she will be informed about the trial by a surgeon or physician. If the patient is interested in participation, the course of the trial will be explained in detail to the patient, and the investigator inquires whether all inclusion and exclusion criteria are met. If this is the case, the patient will receive a printed version of the patient information and the informed consent form. The informed consent form has to be signed and returned no later than on the day before surgery.

After surgery, the inclusion criteria will be checked again (no change in the planned course of surgery), and if all criteria are fulfilled, the patient will be randomized to receive capsules containing either 100 mg caffeine, 200 mg caffeine, or placebo (corn starch) (Fig. 1).

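### The arrhythmia exclusion is narrower than the protocol's own caffeine caution, so a known, silent, untreated tachyarrhythmia does not bar entry (low severity)

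*Protocol article*

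**What the plan says.** The Patient safety section of the protocol article lists the documented side effects of caffeine and adds a dose caution: "Doses of 100 mg are not recommended in the case of tachyarrhythmia and liver cirrhosis". The caution is not limited by symptoms or treatment. The next sentence reads: "All these side effects and restrictions have been considered in the exclusion criteria".

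The list under Study population excludes cardiac arrhythmia when it is clinically significant. A bracket defines that as causing the patient physical complaints or requiring regular medication. The criterion that follows gives the purpose of both: "Cardiac insufficiency (like the previous criterion as safe guard against the effects of caffeine".

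Under Study design, the two active arms receive caffeine 100 mg or 200 mg three times daily.

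Once treatment has begun, the section on withdrawal and stopping medication ends it under several conditions. One is: "Tachycardia, defined as a pulse of over 120/min three times within 1 hour, occurs". Another is the investigator's opinion that "continuation of the treatment is detrimental to the patient"'s well-being. The sections on data collection and on patient safety describe continuous inpatient supervision.

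**The concern.** The caution, as worded, covers every tachyarrhythmia. The exclusion covers only arrhythmia that the patient feels or takes regular medication for. A patient known to have a tachyarrhythmia who has no complaints and takes no regular medication falls under the caution but not under the exclusion.

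What is at stake is the safety of an occasional participant. Someone for whom the protocol's own safety text advises against 100 mg could receive that dose, or twice that dose, three times a day. The Patient safety section also notes that few data exist on caffeine in the elderly and none on its use directly after abdominal surgery, which is a reason to apply the caution at entry. No statistical quantity is involved.

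**Working it through.** No plan figure needs reproducing. The check is a comparison of texts, made in four steps.

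1. **Scope of the caution (Patient safety).** Any tachyarrhythmia, at 100 mg.

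2. **Scope of the exclusion (Study population).** Arrhythmia with physical complaints or with regular medication. What remains uncovered is a known tachyarrhythmia with neither.

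3. **Whether anything else covers the remainder.** The article lists 3 inclusion criteria, 15 exclusion criteria and 2 checks at the end of surgery: 3 + 15 + 2 = 20 conditions.
   - One exclusion names arrhythmia, with the limit in step 2.
   - Cardiac insufficiency and ASA class IV or V are different conditions. A silent, untreated tachyarrhythmia need not meet either.
   - The list contains no general exclusion at the investigator's discretion.
   - The end-of-surgery checks are "No major change of the planned surgery" and "No epidural anesthesia used during or after surgery". Neither concerns heart rhythm.
   - The Study outline describes the repeat check in the same terms: "After surgery, the inclusion criteria will be checked again (no change in the planned course of surgery".

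   None of the 20 conditions covers this patient. The count shows only that the search was complete. It does not measure harm.

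4. **Dose reached.** Relative to the cautioned single dose, the arms give 100/100 = 1 times and 200/100 = 2 times. Per day this is 3 × 100 = 300 mg or 3 × 200 = 600 mg, up to the limit of ten capsules. These figures show that the caution applies to both active arms. They say nothing about how often an event would occur.

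**Safeguards after entry.** The tachycardia rule needs three readings above 120/min within one hour, whereas the Endpoints section says pulse is usually recorded three times daily. The routine schedule alone would therefore not trigger the rule; someone must be prompted to measure again. The investigator's discretion and inpatient supervision can prompt that. All of these act only after caffeine has been given.

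**The case against.** The strongest reply is that nothing here is an error. The safety text says the restrictions were considered. It does not say that each was adopted in full or that every affected patient is excluded. The arrhythmia criterion carries its own definition, and the neighbouring criterion states its purpose, which suggests a chosen threshold. The article need not print the reason; the full protocol may give it. The caution is a recommendation summarised in one sentence from a cited source, and whether that source meant silent, untreated arrhythmia cannot be checked here.

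Much of this stands. A reader might infer that the protocol contradicts itself, or that it promises to exclude all tachyarrhythmia and fails to do so. The documents do not support that reading, because having considered a restriction is compatible with setting a limit on it. Nor should the cirrhosis criterion be used as a contrast, since its MELD bracket could be read as a qualifier too.

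It is also fair to say that exposure is modest and supervised. The article equates 100 mg with about one cup of filtered coffee, bars other caffeine during treatment, limits treatment to ten capsules, provides emergency unblinding, and has an independent committee review safety after 60 patients. These points keep the severity low.

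The reply does not remove the gap between the two printed texts. If the threshold is deliberate, the article gives no reason for it, and the safeguards listed do not operate at entry.

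**Conclusion.** The point holds as a low-severity safety alignment. As written, the criteria allow a patient with a known, asymptomatic, untreated tachyarrhythmia to be randomised to caffeine doses that the Patient safety section advises against. This may be intended.

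The affected group is very small: a known tachyarrhythmia, no complaints, no regular medication, no cardiac insufficiency, and not ASA IV or V. The article gives no frequency and none is assumed, so it is not shown that any of the 180 patients would fall into the group.

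A reader might go on to infer a threat to the trial's validity. There is none: sample size, alpha, power and the pooled comparison of caffeine with placebo do not depend on this criterion. The conclusion rests only on the wording of the article and not on the source cited for the caution.

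**What to change.** Reword the arrhythmia exclusion under Study population to: *any known tachyarrhythmia, or other clinically significant cardiac arrhythmia (physical complaints or regular medication)*. This applies to known cases only, and no ECG or other rhythm screening is added.

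The cost is a one-line amendment and at most a few fewer eligible patients. The Trial status section reports 12 patients randomised by 7 March 2016, so at that date the change would have applied to the remaining 180 − 12 = 168 places.

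If the present threshold is deliberate and is to be kept, the lesser alternative is one sentence in the Patient safety section stating that only clinically significant arrhythmia is excluded, and why. That makes the choice clear but leaves the entry gap open, so the rewording is preferred.

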### Publication

The results of this trial are intended for publication in a peer-reviewed medical journal independently of the outcome of the trial. Trial participants will be provided with a German summary of the trial results or a copy of the final publication if they expressed their interest on the informed consent form to receive one or both of these documents.

## Discussion

A previous study showed that postoperative coffee consumption shortens the time to first bowel movement after colorectal resections [10]. As outlined in the Background section, it is highly unlikely that this effect is due to the physical properties (temperature, osmolality, or volume) of the coffee. Much more likely, one (or more) of the numerous phytochemicals of the coffee bean are responsible for the effect. The most obvious candidate seems to be caffeine, the most popular and probably best-researched component of the coffee. However, very little evidence exists that caffeine was responsible for the observed effect in the study by Müller et al. [10]. Rao et al. reported that the effect of caffeinated coffee on colonic function is stronger than decaffeinated coffee; however, even decaffeinated coffee had an effect on the colonic function [9]. Whether this effect was due to the low amount of caffeine still present in the decaffeinated coffee or due to another substance is unknown. Thus, we agree that our hypothesis for this trial is rather speculative. Nevertheless, the safety profile of caffeine is well documented, and the substance is part of the daily diet of most people in the Western world. In case our study hypothesis should be wrong, the risk of doing harm to the study participants is extremely low. Therefore, we think this study is ethically acceptable, particularly considering that, if the hypothesis were proven, a cost-effective and well-accepted drug with little side effects would be available to ameliorate postoperative bowel paralysis.

### Trial status

Since 1 August 2015, the trial is open for recruiting, and so far, 12 patients have been randomized (as of 7 March 2016).

## Abbreviations

AES: advanced encryption standard (current approved and standard algorithm for data encryption)
ASA: American Society of Anesthesiologists, here used as an acronym for the ASA physical status classification system
CRP: C-reactive protein
CT: computed tomography
NRS: numeric rating scale
